### Outcomes and measurements

Sociodemographic data (including participant sex, age, height, weight, BMI, smoking status, educational level, employment situation, pain duration and medication intake) will be collected prior to the implementation of the prehabilitation programme. Additionally, information will also be gathered on the education level, employment status, duration of symptoms, medication use, and level of physical activity the patients engage in.

### Primary outcome

The primary outcome, the degree of disability, will be measured using the Spanish version of the Oswestry Disability Index (ODI) [26] which has been validated for measuring disability in the Spanish population with LBP and in Spanish patients that have previously undergone lumbar disc surgery [27]. The ODI is widely used in the fields of neurosurgery and spine surgery [28] and is considered the gold standard test for measuring disability. The ODI comprises a total of 10 items that ask about pain intensity, personal care (bathing, dressing, and so on), lifting, walking, sitting, standing, sleeping, sex life, social life, and travelling. Each item has 6 grades, and the higher the score, the more serious the disability. A difference of 15 points has been suggested as the minimum clinically important difference (MCID) for surgical populations [29].

### Secondary outcomes

Pain perception will be assessed using the Spanish version of the Short Form McGill Pain Questionnaire (SF-MPQ) [30] and a numerical rating scale (NRS). The SF-MPQ consists of a 15-point descriptor of average pain, articulated as 11 points of sensory experience and 4 points of affective experience. Together, the sensory and affective pain rating scores give a value for a total pain experience ranging from 0 (no pain) to 45 (maximum pain). Melzack [31] previously showed that the SF-MPQ is a responsive scale that provides both reliable and valid data. The suggested MCID for the SF-MPQ is 5 points [32]. An 11-point (0–10) NRS will also be employed to measure pain intensity, as previously recommended in clinical trials of chronic pain treatments [33]. The NRS will present the numbers 0 to 10 to the patients, where 0 means ‘no pain’ and 10 means ‘the worst pain imaginable’. The participants will be asked to rate their pain by indicating the number that best describes their average pain over the 24 hours prior. The suggested MCID for this variable is 2 points for patients with chronic pain [34].

Health-related quality of life will be measured using the Spanish version of EuroQol-5D (EQ-5D) [35]. The EQ-5D is a self-reported questionnaire comprising 5 dimensions: mobility, self-care, usual activities, pain/discomfort, and anxiety/depression, with each dimension subdivided into 3 levels: ‘no problems’, ‘some problems’, and ‘extreme problems’, indicating the level of function perceived by the patient. Each level carries a weighted score which is combined across the 5 dimensions to reach an overall index score. EQ-5D scores range from −0.5 to 1.0, with negative scores indicating states ‘worse than death’, 0 indicating no quality of life or ‘death’, and 1 indicating full health. The EQ-5D has previously been used as an outcomes indicator in patients with lumbar pain [19, 36].

The Spanish version of the Fear-Avoidance Beliefs Questionnaire (FABQ) [37] is a self-reported questionnaire consisting of 16 independent sentences rated by the participant on a 7-point Likert scale ranging from 0 (‘completely disagree’) to 6 (‘completely agree’), with higher scores reflecting higher levels of fear-avoidance beliefs. The questionnaire contains 2 subscales: the FABQ-Work (ranging from 0 to 42 points) and FABQ-Physical Activity (ranging from 0 to 24 points), which assess the patient’s attitudes and beliefs about how occupational or physical activities may influence their LBP, respectively. The suggested MCID value of the FABQ-Physical Activity subscale is 6 points [38]. Moreover, the FABQ has been shown to have good reliability and validity [39].

Kinesiophobia will be measured with the Spanish version of Tampa Scale for Kinesiophobia (TSK-11). This is a self-reported scale in which patients rate 11 statements about their fear of movement on a 4-point Likert scale. This results in a score range of 11 to 44 points, with higher scores corresponding to a greater fear of pain, movement, and injury. The TSK-11 has also been shown to have good reliability and validity [40].

The level of pain catastrophising will be assessed using the Spanish version of Pain Catastrophizing scale (PCS). The PCS measures 3 related constructs of pain catastrophising: magnification, rumination, and helplessness, with a total score ranging from 0 to 52 points. Participants will be asked to score 13 pain-related cognitions on a 5-point Likert scale, where higher scores indicate a higher degree of pain catastrophising. The internal consistency of the Spanish version of the PCS is high (α = 0.94) [41].

Anxiety and depression will be measured with the Spanish version of the Hospital Anxiety and Depression Scale (HADS) [42]. The HADS comprises two 7-item scales designed to rate depression (HADS-D) and anxiety (HADS-A). Each item is scored from 0 to 3, with a score range on each subscale of 0 to 21 points. Scores of 0–7 indicate the absence of anxiety or depression; 8–10 indicate mild levels; 11–14 indicate moderate levels; and 15–21 indicate severe levels of anxiety or depression. The Spanish version has shown suitable levels of reliability (for HADS-D α = 0.82 and for HADS-A α = 0.81).

Physical activity levels will be measured using the IPAQ-SF validated for Spanish. This is a self-administered questionnaire comprising 7 items which collects information about the physical activity the surveyee has engaged in during the 7 days prior. This questionnaire collects information about the days per week and minutes per day the respondents spent engaged in vigorous or moderate exercise, walking, and sedentary activities. The validity of the IPAQ-SF has been shown to be acceptable for the measurement of total and vigorous physical activity and its reliability coefficients for application in the Spanish population were good [43].

Patient satisfaction with the treatment will be assessed using the Patient Global Impression of Change (PGIC) scale to allow them to express their overall impression of how they have changed following the prehabilitation programme. The PGIC is measured on a 7-point Likert scale where 1 represents ‘completely recovered’, 2 is ‘very much improved’, 3 is ‘slightly improved’, 4 corresponds to ‘no change’, 5 is ‘a little worse’, 6 is ‘much worse’, and 7 is ‘enormously worse’. Improvement will be considered with a score of 1, 2, or 3; the absence of change, a score of 4; and scores of 5, 6, or 7 will be considered patient deterioration. Of note, this scale has been consistently employed to evaluate patient satisfaction in cases of chronic lumbar pain [19, 44].

All the primary and secondary variables will be assessed using a form distributed to the participants by email at different points throughout the study (baseline, immediately after the 4-week prehabilitation, and at the 1-month, 6-month, and 12-month post-surgery follow-up assessments). After completion of the prehabilitation programme, it will be verified that participants have not interacted with other participants through a question specifically designed for this purpose in the form. Similarly, participants will also be asked about the number of videos viewed, and their level of assimilation and comprehension will be assessed through a brief quiz on the material’s content.

All the adverse events will be evaluated, recorded, and discussed in the final communication of the study results. The study design and progression of patients through the study protocol are outlined in Fig 1.

**Fig 1 pone.0303979.g001:**
[figure not shown]
Protocol timeline implemented for the study.

### Statistical methods

The sample size has been determined a priori using G-Power software (version 3.1.9.2)(F tests, ANOVA: Repeated measures, within-between interaction). This calculation was based on the results of a similar study evaluating the effects of a prehabilitation programme in patients with degenerative lumbar spine disorders [19]. In this previous study, an effect size (Cohen *d*) of 0.3 was observed in the primary variable (measured using the ODI) after completion of the preoperative treatment. Therefore, considering an alpha probability of 0.05, an observed power of 0.9, and the effect size found by Lindbäck et al. (*d* = 0.3), we determined that the inclusion of a total of 82 participants will be required. However, to account for potential losses, we will increase the sample size by 20%, meaning that a total of 100 patients will be included in this work, 50 in each group.

The statistical analysis will be conducted by taking an intention-to-treat approach. Missing data will be handled using the multiple imputation method, on the assumption that values at each time point follow a specific distribution. For between-group comparisons of demographic data, unpaired Student *t*-tests or Mann–Whitney U tests will be used for continuous variables and chi-squared tests will be employed for categorical variables. Two-way analysis of covariance and repeated measures (with age and sex as covariates) will be used to compare the effects of the interventions in each group over time. Analysis of covariance will be adjusted for baseline values. A confidence interval of 95% will be used to establish differences and statistical significance will be reported for all between-group differences at *ρ* < 0.05. Cohen *d* effect sizes will also be calculated for changes in groups over time, where a Cohen *d* of 0.20 will be considered a small, 0.50 a medium, and 0.80 to infinity a large effect size, respectively [45]. All the statistical analyses will be performed using SPSS software for Windows (version 27.0, IBM. Corp., Armonk, NY).

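### Eighty-two patients do not give 90% power at Cohen d = 0.3: the calculation most probably entered d/2 = 0.15 as the interaction effect, which corresponds to a group difference of about 0.7 SD

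*Protocol article*

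**What the plan says.** All the inputs are in the protocol article under Statistical methods.

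- Test: "F tests, ANOVA: Repeated measures, within-between interaction", run in G*Power.
- Planning effect, from an earlier prehabilitation trial: "an effect size (Cohen *d*) of 0.3 was observed in the primary variable (measured using the ODI) after completion of the preoperative treatment". It therefore belongs to one time point.
- Error rates: "considering an alpha probability of 0.05, an observed power of 0.9".
- Result: "we determined that the inclusion of a total of 82 participants will be required".
- Allowance for losses: "we will increase the sample size by 20%, meaning that a total of 100 patients will be included", with "50 in each group".

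The paragraph gives no Cohen f, number of measurements, correlation among measurements or sphericity correction. The sections on blinding and on secondary outcomes list five assessments: baseline, end of prehabilitation, and 1, 6 and 12 months after surgery. The planned analysis is a repeated-measures analysis of covariance adjusted for baseline.

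**The concern.** A standardised two-group difference of 0.3 is small, and 41 patients per arm is far fewer than such a difference usually needs for 90% power. Repeated measurements can help, but the named G*Power module does not take Cohen d. It takes Cohen f for the group-by-time interaction. The familiar rule f = d/2 is the conversion for a main effect of two groups and does not carry over to the interaction.

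This paragraph is the only justification given for the trial's size, and it concerns the primary outcome. If it stands, readers will take the trial as having 90% power for a small effect and will give a non-significant result more weight against d = 0.3 than the design supports.

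**Working it through.** **Formulae.** The interaction test (k = 2 groups, m measurements, correlation rho) uses a noncentral F with lambda = f² × N × m / (1 − rho), df1 = m − 1 and df2 = (N − 2)(m − 1). Where a sphericity correction epsilon is used, it multiplies lambda and both df.

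**1. Reproducing 82.** The values of m and rho are my assumptions, because the article does not print them.

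- f = 0.3/2 = 0.15, m = 4, rho = 0.5, epsilon = 1: lambda = 0.0225 × 82 × 4 / 0.5 = 14.76 on 3 and 240 df, power 0.9075. N = 80 gives 0.8998, so the smallest balanced N is exactly 82.
- f = 0.15, m = 5, rho = 0.5: N = 70 with epsilon = 1, and 82 with epsilon = 0.8.
- f = 0.30 entered directly, m = 2 to 5, rho = 0 to 0.8: N = 10 to 62, never 82.
- G*Power's option for effect sizes as in SPSS: N = 46 to 122 (f = 0.30) or 176 to 472 (f = 0.15) over m = 2 to 5. None is 82; the nearest is 74.

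Every run of the named test that returned 82 used f = 0.15.

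**2. What f = 0.15 means as an interaction.** Take equal baselines and a constant difference of d SD at every later visit. The interaction deviations are half the departures of the visit-specific differences from their mean, so f = (d/2) × sqrt(m − 1) / m.

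| | m = 4 | m = 5 |
|---|---|---|
| f per unit d | 0.2165 | 0.200 |
| f at d = 0.3 | 0.065 | 0.060 |
| d implied by f = 0.15 | 0.69 | 0.75 |

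A difference present at one post-baseline visit only gives the same f.

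**3. Power at d = 0.3 with N = 82.**

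*Interaction.* For m = 4 and rho = 0.5, lambda = 0.065² × 82 × 4 / 0.5 = 2.77 (unrounded f), against 14.76 above.

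| rho | m = 4 | m = 5 |
|---|---|---|
| 0.3 | 19% | 18% |
| 0.5 | 25% | 24% |
| 0.7 | 40% | 39% |
| 0.8 | 58% | 56% |

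*Two-sample t-test at one visit.* Noncentrality 0.3 × sqrt(41/2) = 1.36, power 27%.

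*ANCOVA at one visit.* The residual SD is multiplied by sqrt(1 − r²). Power is 34% (r = 0.5), 47% (r = 0.7) and 61% (r = 0.8).

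*Baseline-adjusted average of four post-baseline visits, constant 0.3 SD.* With equal correlations the SD factor is sqrt((1 + 3r)/4 − r²): 0.612, 0.534 and 0.458 for r = 0.5, 0.7 and 0.8. Power is 59%, 71% and 83%.

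**4. Effect detectable with 90% power at 50 per group.**

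| Contrast | Detectable difference |
|---|---|
| One visit, unadjusted | 0.65 SD |
| One visit, ANCOVA, r = 0.5 | 0.57 SD |
| One visit, ANCOVA, r = 0.7 | 0.47 SD |
| Four-visit average, adjusted, r = 0.5 | 0.40 SD |
| Four-visit average, adjusted, r = 0.7 | 0.35 SD |

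**The case against.** **The cause is inferred.** The article does not print f = 0.15, and 4 measurements without sphericity loss is not the only route to 82: 5 measurements with epsilon = 0.8 gives it too. This stands. A reader might infer that the calculation used four measurements and so contradicts the five-visit schedule, but the document does not show that. The entry of d/2 is the most probable explanation and no more. The inconsistency does not depend on it, because section 3 of the working uses only the stated d, alpha and N, with the correlation varied.

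**Power depends on an unstated correlation.** This also stands. There is no single true power, and a narrow band such as 25-40% would be too firm. A condensed article may leave the correlation to a fuller document, so its absence is not itself the fault.

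**The planned analysis may be more sensitive.** The article plans a repeated-measures analysis adjusted for baseline. If the primary contrast were the average over four post-baseline visits with a constant 0.3 SD effect, power at 82 would be 59-83%, and with all 100 patients at r = 0.8 it would reach 90%. It is therefore tempting, but wrong, to say that the trial would miss d = 0.3 more often than not under any analysis. However, the article attaches 90% to 82 patients, names the interaction test, and takes its d from a single time point. Even this favourable reading stays below 90% at 82 for r = 0.5 to 0.8.

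**Conclusion.** The statement that 82 patients give 90% power at d = 0.3 is wrong as written. For the named interaction test, power is about 24-25% at correlation 0.5 and 18-58% over correlations 0.3 to 0.8. For a single-visit comparison it is 27% unadjusted and 34-61% with ANCOVA (r = 0.5-0.8). The four-visit average gives 59-83%. These figures assume equal baselines, a constant post-baseline difference (or, for the interaction, a difference at one visit only), equal correlations and no sphericity loss.

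A reader might go further and conclude that 100 patients are too few or that the trial must be enlarged. The document does not support that: it does not show that 0.3 SD is the smallest effect worth detecting, and 100 patients have reasonable power for larger effects. The fault is a stated sensitivity that the design does not have. It should be corrected before results are read against it.

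**What to change.** Keep 100 patients. Delete the claim of 90% power at d = 0.3, and state the effect detectable at 90% power for the contrast that the trial treats as primary, with the number of measurements and the assumed correlation as part of that figure. Use the row of the last table that matches the contrast; quoting 0.57 SD for a trial whose primary contrast is a four-visit average would understate its sensitivity. If the interaction remains the primary test, derive its f from an explicit pattern of differences over the visits actually analysed. Add a sentence that a null result at a single visit, or for the interaction, would not exclude an effect of d = 0.3.

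The cost is a rewritten paragraph. Recruitment, conduct and analysis do not change. The downside is a less favourable stated sensitivity.

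### The test that the trial is powered on (group by time) does not match its between-group hypothesis, and the term that decides the trial is left open

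*Protocol article*

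**What the plan says.** All of this is in the Protocol article, Statistical methods, unless noted.

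- **Sizing.** The procedure chosen in the sample-size software is "F tests, ANOVA: Repeated measures, within-between interaction". Its error rates are given by the words "considering an alpha probability of 0.05, an observed power of 0.9". The effect is a Cohen d that, in an earlier trial, "of 0.3 was observed in the primary variable (measured using the ODI) after completion of the preoperative treatment". The result: "we determined that the inclusion of a total of 82 participants will be required", raised to 100 (50 per group) for losses.
- **Analysis.** The model is given as follows: "Two-way analysis of covariance and repeated measures (with age and sex as covariates) will be used to compare the effects of the interventions". The comparison runs across the assessments. A separate sentence adds: "Analysis of covariance will be adjusted for baseline values". The text does not say whether baseline is a covariate only, a level of the time factor, or both.
- **Reporting.** 95% confidence intervals are promised, with significance for every between-group difference at 0.05. In addition, "Cohen *d* effect sizes will also be calculated for changes in groups over time".
- **Hypothesis (Introduction, last paragraph).** The video programme is expected to do better than written instructions on disability.
- **Outcome and visits.** Primary outcome defines the ODI as primary without a visit and cites a 15-point minimum important difference. Secondary outcomes lists five assessments: baseline, end of prehabilitation, and 1, 6 and 12 months after surgery.

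**The concern.** A superiority hypothesis on disability needs an estimate of how far apart the arms are in ODI points. A group-by-time interaction asks whether the gap between arms changes over the levels of time. The two questions coincide only for some codings of time and some shapes of effect.

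The coding matters because the analysis is also baseline-adjusted. In the ordinary sense, baseline is then a covariate and time has four post-baseline levels. An equal benefit at all four visits is the interaction's null hypothesis. If baseline is a time level, a sustained benefit does create an interaction, but the F test spreads it over several degrees of freedom and yields no figure to set against 15 ODI points.

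Two things are at stake. A real, lasting benefit could be reported as non-significant because the powered term is the wrong one. Or, with no term fixed, the deciding one could be picked after the results are seen. The effect sizes add to this: both arms have decompression surgery, so a Cohen d computed on change within each arm would largely reflect the operation.

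**Working it through.** **1. Reproducing 82.** For two groups f = d/2 = 0.15. For the within-between interaction, λ = f²·N·m/(1 − ρ), with df m − 1 and (N − 2)(m − 1). The number of measurements m and the correlation ρ are not stated. With m = 4, ρ = 0.5 and sphericity assumed:

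λ = 0.0225 × 82 × 4 / 0.5 = 14.76; df 3 and 240; power 0.9075.

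N = 80 gives 0.8998, so 82 is the smallest balanced N. At ρ = 0.5, m = 2, 3 and 5 give 120, 96 and 70. Four equals the number of post-baseline visits. That fits the covariate reading but does not prove it.

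**2. What f = 0.15 means for an interaction.** With δₜ the standardised group difference at visit t, the interaction has f² = (variance of δₜ over the levels of time)/4.

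- Four post-baseline levels, constant benefit: the variance is 0, so f = 0 and power equals alpha.
- Five levels including baseline, d = 0.3 at all four later visits: variance = 0.09 × 0.8 × 0.2 = 0.0144 and f² = 0.0036, against the 0.0225 used for sizing. At N = 100, m = 5, ρ = 0.5, λ = 0.0036 × 100 × 5 / 0.5 = 3.6. Simulated power there is 28%.

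**3. Power for a constant benefit, 50 per arm.** Assumed correlations: baseline with later visits 0.4, between later visits 0.6. The interaction rows are simulated (4,000 trials). For the contrasts, noncentrality = (d/SD) × √(50/2):

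- one visit: SD = √(1 − 0.4²) = 0.917
- mean of four visits: SD = √((1 + 3 × 0.6)/4 − 0.4²) = √0.54 = 0.735

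| Test | d = 0.3 | d = 0.5 |
|---|---|---|
| Interaction, baseline as covariate, 4 visits | 4–5% | 5–6% |
| Interaction, baseline as time level only | 29–30% | 67–68% |
| Baseline-adjusted difference, one visit | 37% (noncentrality 1.64) | 77% (2.73) |
| Baseline-adjusted difference, mean of 4 visits | 52% (2.04) | 92% (3.40) |

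Simulating the two contrasts gave 35–38% and 76–77% for one visit, and 53% and 91–92% for the mean.

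**4. Sensitivity.** Equal correlations of 0.5 and 0.7, 41 and 50 per arm, 2,000 trials per setting:

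- Baseline as covariate, four visits: the interaction rejects 4–6% at d = 0.3, 0.5 and 0.8. The group term of the same model has 59–79% power at d = 0.3 and at least 95% at d = 0.5.
- Baseline as time level only: the interaction has 24–48% at d = 0.3 and 58–92% at d = 0.5.
- Baseline as both level and covariate: 27–57% and 68–97%. This can exceed the one-visit contrast but stays below the averaged one (at 50 per arm and d = 0.3, 30–57% against 67–79%).
- Transient effect (0.5 at the first visit, then 0), covariate coding: the interaction has 61–91%, the group term only 14–22%.

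**5. The stated 90% restated for a between-group contrast, d = 0.3, 100 patients.** One visit: 32% unadjusted; 41% and 56% with baseline correlation 0.5 and 0.7. Mean of four visits: 69% and 80%. For 90% power the totals are 468 unadjusted at one visit, 352 and 240 adjusted, and 176 and 134 for the mean.

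**The case against.** The strongest reply is that the article never calls the interaction its decision test. The phrase appears only in the sample-size sentence. The analysis text promises between-group differences with 95% confidence intervals from a baseline-adjusted model. The averaged contrast is also already in that model: with baseline as covariate and four post-baseline visits, the group term is the baseline-adjusted comparison of post-baseline means. The alpha-level figure needs three conditions together that the text does not state: baseline as covariate only, four time levels, and only the interaction counting. A constant benefit is also the least favourable shape for that test; for an early effect that fades, the interaction does better than the average. The Cohen d wording does not say outright that it is within-arm, and nothing makes it decisive. Model class and covariance structure belong to an analysis plan.

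Most of this stands, and it rules out a stronger reading. A reader might infer that the trial cannot detect a sustained benefit, or that no between-group estimate is planned. The documents support neither.

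The reply does not close the gap. The interaction is the only test given an alpha, a power and an N. Reporting every between-group difference, over four post-baseline visits, does not say which one decides. The article itself chose both the powered test and the baseline adjustment, so their poor fit is not a detail deferred to another document.

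**Conclusion.** The point holds in a limited form: the powered test does not match the hypothesis, and the deciding term is open.

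On the covariate reading, the powered interaction is blind to a constant benefit of any size (4–6% rejection). With baseline as a time level only, it detects one, with about 68% power at d = 0.5 and 50 per arm, against about 77% for a one-visit adjusted contrast and 92% for the average. These figures rest on assumed correlations of 0.4 and 0.6 and a benefit equal at all four visits. If baseline is both level and covariate, only the averaged contrast is consistently stronger.

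The 90% does not carry over to the hypothesis. At d = 0.3 with 100 patients, a between-group contrast has about 37% power at one visit and 52% averaged under those correlations, or 32% to 80% across the wider assumptions.

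That four measurements reproduce 82 should not be read as proof that time excludes baseline.

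**What to change.** Revise Statistical methods as follows.

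1. Use baseline ODI as a covariate only, with the post-baseline visits as outcomes.
2. Name one primary test: the between-group ODI difference adjusted for baseline, age and sex, either at one visit named in advance or averaged over the post-baseline visits. Choose by the effect expected; averaging suits a sustained benefit and serves a transient one poorly.
3. Report it in ODI points with its 95% CI, beside the 15-point difference the article cites.
4. Keep the group-by-time interaction as a secondary test of whether the effect changes.
5. Compute Cohen d from the adjusted between-group difference, not from change within arms.
6. Restate the power for the named contrast, with the assumed correlation.

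A mixed model or ANCOVA would serve; that choice and the covariance structure can be left to the analysis plan. The cost is rewording and a new power calculation in the same software, with no extra data. The restated power will be below 90% at d = 0.3 with 100 patients, and the investigators must then accept that or revisit the sample size.

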## Abstract

The aim of this present clinical trial is to evaluate the effectiveness of a multicomponent prehabilitation programme administered through educational videos versus another programme based on written exercise recommendations, in patients scheduled for lumbar radiculopathy surgery. This study will be a multicentre, controlled, randomised, parallel clinical trial. One hundred participants undergoing lumbar radiculopathy surgery who meet the established inclusion criteria will be recruited at different Spanish hospitals. The experimental group will follow a 4-week prehabilitation programme combining therapeutic exercise, back care education, and pain neuroscience education delivered through videos designed for consumption at home. The control group will be provided with written instructions to perform therapeutic exercises during the same prehabilitation time period. The primary outcome of the study will be disability, assessed using the Spanish version of the Oswestry Disability Index. The secondary outcomes will be pain perception, health-related quality of life, fear avoidance, kinesiophobia, catastrophising, anxiety, depression, physical activity, and the treatment satisfaction of the patients. This study will provide evidence for the effectiveness of a home-based multicomponent prehabilitation programme that addresses some already identified barriers to patient attendance in face-to-face programmes. Understanding the medium and long-term effects of pre-surgery lumbar muscle training and pain neuroscience education administered via instructional videos watched by patients at home, will help improve the design of prehabilitation programmes in this population while also improving the cost-effectiveness of such interventions.

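### The primary ODI outcome has no named time point or contrast, and the 0.05 rule covers every between-group difference without a gate or adjustment

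*Protocol article*

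**What the plan says.** The outcome is defined without a time point in both places where it appears. The Abstract says: "The primary outcome of the study will be disability, assessed using the Spanish version of the Oswestry Disability Index". The Primary outcome section says: "The primary outcome, the degree of disability, will be measured using the Spanish version of the Oswestry Disability Index (ODI").

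The end of the Secondary outcomes section sets one schedule for all primary and secondary variables: "baseline, immediately after the 4-week prehabilitation, and at the 1-month, 6-month, and 12-month post-surgery follow-up assessments". That gives four ODI assessments after baseline, one before surgery and three after it.

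Statistical methods sizes the trial on an omnibus test ("F tests, ANOVA: Repeated measures, within-between interaction"), "considering an alpha probability of 0.05, an observed power of 0.9" and an effect of d = 0.3. The effect comes from an earlier study's ODI result at the end of its preoperative treatment. The required total is 82, raised to 100. The planned analysis is a repeated-measures analysis of covariance over time, adjusted for baseline. The decision rule reads: "statistical significance will be reported for all between-group differences at" p < 0.05.

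No section names a primary contrast, an order of testing, a gate or a multiplicity adjustment.

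**The concern.** Disability just before decompression and disability a year after it are different claims about the programme, and the protocol leaves open which one is primary. The sources that could settle it point in different directions: the effect size comes from the end of preoperative treatment, the sample size rests on a test tied to no visit, and the Abstract and Discussion stress later outcomes as well.

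A detail left to an analysis plan would not be a finding. Here, however, the time point belongs to the definition of the primary outcome, and the article itself states a significance rule that covers all differences. Applied as written to the four ODI visits, that rule does not hold the 5% error rate on the primary outcome. The result to be emphasised could also be chosen after the data are seen.

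**Working it through.** **Inputs.** From the protocol: four ODI visits after baseline; alpha 0.05; power 0.90; d = 0.3; N = 82, then 100 (50 per arm). Not in the protocol, and therefore assumed: the correlation between visits, the number of measurements entered in the sample-size calculation, and the correlation of ODI with its baseline.

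**1. The plan's own figure.** For a within-between interaction with two groups and no sphericity correction:

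- f = d/2 = 0.15
- λ = f² × N × m / (1 − ρ), df1 = m − 1, df2 = (N − 2)(m − 1)
- With m = 4 and ρ = 0.5 (both assumed): λ = 0.0225 × 82 × 4 / 0.5 = 14.76, df = 3 and 240, power = 0.908. N = 82 is the smallest even total that reaches 0.90.
- With m = 5, the number of assessments listed, the total would be 70.
- Loss allowance: 82 × 1.2 = 98.4, consistent with 100.

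So N = 82 is reproduced, as the size for an omnibus group-by-time test and not for a comparison at one visit.

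**2. Four visits, each tested at 0.05 with no gate.** If independent: 1 − 0.95⁴ = 0.185. With four equally correlated normal statistics under no effect (simulation), P(any |z| > 1.96) is:

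| Correlation between visit statistics | P(at least one p < 0.05) | Multiple of 0.05 |
|---|---|---|
| 0 | 0.185 | 3.7 |
| 0.3 | 0.174 | 3.5 |
| 0.5 | 0.156 | 3.1 |
| 0.7 | 0.130 | 2.6 |
| 0.9 | 0.094 | 1.9 |

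Simulating 100 patients with baseline-adjusted ANCOVA at each visit gives 0.184, 0.171, 0.165 and 0.162 for between-visit correlations of 0.3, 0.5, 0.7 and 0.85. Adjusting for baseline removes part of the shared variation, so high correlation between visits helps less than the table suggests.

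**3. The same visits behind a gate.** In the same simulations, under no effect at any visit:

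- Visits read only after a significant group-by-time interaction: about 0.04.
- Visits read if either the overall group effect or the interaction is significant: about 0.07 to 0.08.

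**4. Power if one visit is made primary.** Two-sample comparison, d = 0.3, two-sided 0.05:

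- Unadjusted, 50 per arm: noncentrality 0.3 × √(50/2) = 1.50, power about 32%. With 41 per arm, about 27%. For 90% power the total is about 468.
- Baseline-adjusted, 50 per arm, effective d = 0.3/√(1 − r²): r = 0.5 gives 0.346 and power about 40%; r = 0.7 gives 0.420 and power about 55%.

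**The case against.** The strongest reply is that the planned model is a repeated-measures analysis, and that the trial was sized on its interaction. That is one test per outcome. If visit contrasts are secondary to it, the error on ODI is about nominal. The significance sentence can also be read as a reporting threshold and not as a definition of trial success, since the protocol states no success criterion at all.

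Much of this stands. A reader might infer that the protocol lets any one visit establish effectiveness, or that its false positive rate simply is three times nominal. The text says neither. The inflation is conditional on ungated testing, and its size depends on an unstated correlation. What does not stand is that the omnibus test already protects the visits: no sentence makes it the primary test or a condition for reading them, and the significance rule covers all between-group differences.

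Two further readings are tempting and should not be pressed. One is to multiply scores by visits, giving about 48 comparisons and a 91% chance of some false positive. The protocol does not say that every score is tested separately at every visit, the 91% requires independence between overlapping scales in the same patients, and multiplicity for secondary outcomes is commonly left to the analysis plan. The other is to call the Abstract's interest in later effects a contradiction; it agrees with the follow-up schedule.

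**Conclusion.** The point holds in conditional form. The primary outcome lacks a time point or contrast, and the stated 0.05 rule has no gate or adjustment. With ungated tests at the four ODI visits, the chance of at least one false positive is about 9% to 19%, and about 16% at a correlation of 0.5, the value that also reproduces N = 82 (with four measurements). With a gate on the group-by-time test it is near 5% when there is no effect at any visit; the text allows this reading but does not require it.

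The figures assume normally distributed statistics and no effect at any visit. They leave out the partial or interim analyses mentioned under Randomisation and blinding, for which no alpha rule is given.

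**What to change.** In Statistical methods and in the registry, before outcome data are analysed, declare one primary ODI test at two-sided 0.05. There are two workable choices.

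- **Group-by-time interaction as the primary test.** This matches the sample size. Claim visit-specific ODI differences only if the interaction is significant, and then with Holm adjustment. State which assessments enter the test. If baseline is used only as a covariate, an interaction over the post-baseline visits alone would not detect a group difference that is constant across them.
- **One named visit as the primary test.** Give the reason for choosing it and restate the power: about 32% unadjusted at d = 0.3 with 50 per arm, or about 40% to 55% with baseline adjustment if the baseline correlation is 0.5 to 0.7. A fixed testing order starting from a single visit carries the same cost, because a failed first step closes all later ones.

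Report secondary outcomes as adjusted differences with 95% confidence intervals, labelled exploratory.

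The cost is a few sentences and a registry update; the Data management section already commits to communicating important modifications to the registry and the journal. The price in claims is real: individual visits and secondary outcomes can no longer be claimed on their own, and a single-visit primary has far less power than the stated 0.9.
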